### Ethics and trial registration

The patients who meet the inclusion criteria will be completely informed about the study protocol. The protocol of this study was approved by the Medical Ethics Committee of National Institute for Medical Research Development (NIMAD), and is in conformity with the Declaration of Helsinki (approval number: IR.NIMAD.REC.1398.181). Each participant will sign the informed consent form. This clinical trial was registered on Iranian Registry of Clinical Trials (IRCT registration number: IRCT20090822002365N23) which is available online (http://irct.ir/user/trial/20288/view).

### Sample size

To estimate the sample size, we considered α = 0.05 and β = 0.20 in line with previous trials. In addition, we used 1570.5 ng/ml as the standard deviation and 1250.0 ng/ml as the mean of hs-CRP levels as the primary variable, as described previously [47]. This resulted in a requirement of 25 participants in each group. To allow for attrition, 27 participants will be recruited for each group, giving a total of 108 obese women.

### Randomization

Randomization to the different treatment arms will be performed using computer-generated random numbers. The 108 participants who meet the criteria will be allocated as such into four treatment groups: 50,000 IU vitamin D soft gel (weekly), plus a 250-mg magnesium tablet (daily); 50,000 IU vitamin D soft gel (weekly) plus a magnesium placebo (daily); vitamin D placebo (weekly) plus a 250-mg magnesium tablet (daily); and a vitamin D placebo (weekly) plus a magnesium placebo (daily). The vitamin D soft gels and magnesium tablets are provided by Zahravi, Iran and Jalinous, Iran, respectively. The placebos for vitamin D and magnesium contained oral paraffin and maltodextrin, respectively, and are supplied by Zahravi, Iran (these were matched in appearance of the corresponding soft gels and tablets). Patients will receive verbal and written counseling on how to consume the supplements and compliance will be evaluated by tablet count every 2 weeks.

For blinding, a person who is not involved in the study protocol will create a randomized list assigning participants to each treatment arm. The soft gels, tablets, and corresponding placebos will be placed into unlabeled identical containers. The study leader will label the containers with participant numbers using the codes generated through the randomization. All investigators and participants will be blinded.

Women who meet the inclusion criteria will be informed completely about the protocol of the study. The ethics committee will review and approve the final study protocol. Each participant will sign the informed consent form.

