## Methods

### Design

We will conduct an 8-week, double-blind, randomized controlled trial in a factorial design. Participants will be recruited from staff at the Iran University of Medical Sciences through advertisements. The trial will be conducted over 8 weeks to evaluate the effects of vitamin D_3_ (50,000 IU, one dose weekly) and magnesium (250 mg magnesium oxide, one dose daily) in obese women. The output measures will be behavioral readouts of mood, circulating levels of BDNF, cytokines, and SIRT1 (Figs. 1 and 2). The protocol is written in line with the Standard Protocol Items: Recommendations for Interventional Trials (SPIRIT) checklist (Additional file 1).

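### The study leader numbers unmarked containers from the randomization codes with no masking described, so the procedure as written does not support the claim that all investigators are blinded

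*Protocol article*

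**What the plan says.** The blinding procedure is in the Randomization section of the protocol article, and it has four parts.

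- The list: "a person who is not involved in the study protocol will create a randomized list assigning participants to each treatment arm".
- The packaging: "The soft gels, tablets, and corresponding placebos will be placed into unlabeled identical containers". Of the placebos, the section says that "these were matched in appearance of the corresponding soft gels and tablets".
- The labelling: "The study leader will label the containers with participant numbers using the codes generated through the randomization".
- The claim: "All investigators and participants will be blinded".

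The Design section uses the same label for the whole trial: "We will conduct an 8-week, double-blind, randomized controlled trial in a factorial design". The article does not say what form the codes take, who fills the containers, who holds the key, or whether the study leader sees the list. It also does not say whether the study leader counts as an investigator, though that is the ordinary reading.

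**The concern.** The plan brings in an outside person, expressly for blinding, to separate the allocation list from the trial team. It then gives the step that joins participant to container to the person who leads the trial. That weakens the separation just set up, and the statement that follows admits no exception.

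Two protections are at stake. The first is allocation concealment: anyone who can see upcoming assignments while women are still entering could influence who enters next. The second is blinding during follow-up. Counselling and the two-weekly tablet counts (Randomization) involve contact between staff and participants, and the counts feed the 90% compliance rule (Participants). The BDI, the 24-hour dietary recalls and the physical activity questionnaire (Outcome measures) rest on what participants report, and waist circumference is read by a person. These are more open to influence than serum assays. The concern depends on whether the study leader has any part in these steps, which the article does not state.

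**Working it through.** No figure in the plan bears on this point, so the check is a reading of the Randomization section in sequence.

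1. **What distinguishes one container from another before labelling?** The containers are identical and carry no label, and each placebo looks like its active product. A soft gel can be told from a tablet, but active cannot be told from placebo by eye.

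2. **What does correct labelling need?** To put a given participant's number on the right container, the labeller must match that participant's assignment to the container's contents, or at least to a set known by some code. A random list plus unmarked containers is not enough without that link.

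3. **Who makes the link, and from what?** The study leader, from the randomization codes. The only list described assigns participants to treatment arms.

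4. **What would the study leader then know?** This depends on the form of the codes, which is not stated.
   - *Codes that identify the treatment.* The study leader can know what each labelled participant receives. The blinding statement then fails for the study leader.
   - *Neutral arm codes, key held outside.* The study leader does not learn the treatment but knows which participants share an arm. The Sample size section plans 27 women in each of four groups (4 × 27 = 108). If one woman's treatment became known, the same code would reveal that of up to 27 − 1 = 26 others. Serum 25(OH)D and magnesium, both trial measurements, could hint at what a code means to anyone who holds the grouping and sees the results. The article does not say whether the study leader sees them.
   - *A different neutral code for every participant, already on each set.* The study leader would learn nothing. This needs sets that are coded before they reach the study leader, whereas the text calls the containers unlabeled.

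5. **Does the text choose among these?** No. The reading that fully protects blinding needs a step the article does not describe and that sits awkwardly with the one it does. The other two leave the study leader with knowledge of the allocation or of its grouping.

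6. **Which outcomes are exposed?** Serum hs-CRP, used for the sample size, is measured by an immunoturbidimetric method, and BDNF, TNF-α, IL-6, sirtuin 1 and 25(OH)D by ELISA. A person's knowledge of the allocation has little route into these readings. The BDI, dietary recalls, activity questionnaire, waist measurement and tablet counts have more. The article gives nothing from which to compute a bias for either set.

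**The case against.** The strongest reply is that the adverse reading is an inference. The article says codes, not arm names, and nowhere says that the list or the key passes to the study leader. With neutral codes and the key kept outside, the study leader could label the containers without knowing any treatment, and the blinding statement could be true as far as treatment goes. Details of code format and key holding are also what a full protocol usually carries, and a protocol version 2 is cited but not shown.

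The consequences can be disputed too. The article gives the study leader no stated role in enrolment, counselling, tablet counts, BDI administration or analysis. The BDI reflects the answers of participants who are themselves blinded, so a labeller's knowledge could reach it only indirectly. The compliance rule has a numeric threshold, which leaves room for influence in the counting but not in the cut-off. The Objectives section names the confounders to be measured, and nothing says that the study leader chooses among them.

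Most of this stands, and it limits the point. It does not remove it. The article does not merely omit the labelling step. It states the step and gives it to the trial's leader, so this is a weakness in a stated procedure. Neutral arm codes would still disclose who shares an arm.

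**Conclusion.** The procedure as written does not support the statement that all investigators will be blinded, and it should be corrected. The conclusion rests on two assumptions: that the study leader is an investigator, and that the containers reach the study leader as described, with no prior code on them.

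A reader might go further and infer that the study leader learns the allocation, that all 108 assignments are visible, that the two sentences cannot both be true, or that the double-blind label is false. The documents do not support any of these as fact. Each holds only if the codes are unmasked, which is not stated. Even then, participants and those who assess outcomes could remain blinded. Nor do the documents show selection bias or biased assessment, because they do not say what the study leader does at entry or follow-up.

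The size of any effect cannot be computed. It would fall mainly on the BDI and other reported measures, and less on the laboratory outcomes, including hs-CRP.

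**What to change.** Have the outside person who creates the list also put the participant numbers on the containers and keep the key until database lock. The study leader then receives only pre-numbered sets, which protects both concealment and blinding whatever form the codes take. The Randomization section should say who numbers the containers, who holds the key and when it is released. If masked codes are already in use, it should say so and state their form.

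The Trial status section has recruitment beginning on 20 October 2019 and ending on 20 December 2020, so some women may already have been enrolled under the present procedure. For them, record what the study leader could see (treatment, arm grouping or neither) and from what date, and report it with the results.

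The cost is small. One task moves to a person already in the plan, with no extra staff and no change to the design, sample size or analysis.

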### Outcome measures

Mood will be assessed using the validated Iranian version of the Beck Depression Inventory (BDI) [48] at baseline and after the intervention period. Blood samples will be collected at both time points after a 12-h overnight fast. Serum will be prepared according to standard protocols and stored at –80 °C until analyses. Serum 25(OH)D will be measured by enzyme-linked immune sorbent assay (ELISA) using the Euro Immun kit (Euro Immun, Germany). Serum magnesium will be determined using a spectrophotometric method with an autoanalyzer (Hitachi 912; Roche Diagnostics). Serum BDNF will be assessed by ELISA using the ZellBio kit (ZellBio, Germany). Serum hs-CRP values will be measured using an immunoturbidimetric method (Pars Azmun, Iran). Serum TNF-α and IL-6 levels will be assessed by ELISA using the Bender Med kit (Bender Med, Germany). Sirtuin 1 will be evaluated using ELISA with the ZellBio kit (ZellBio, Germany).

A questionnaire regarding patient medications and probable supplement use will be recorded at the beginning of the intervention. Dietary intake will be evaluated by 3 days of 24-h recall questionnaires (2 week days and 1 weekend day) at baseline and at the end of the intervention, and total energy and macronutrient intake will be estimated using Nutritionist ӀV software. Physical activity levels will be assessed using the short form of the International Physical Activity Questionnaire (IPAQ) at baseline and at the end of the intervention. Physiometric measures will be taken after overnight fasting, with minimal clothing and without shoes, at baseline and after the intervention. Body weight will be measured with an accuracy of 0.1 kg using the Beurer scale (Beurer, Germany). Height will be assessed using a stadiometer to the nearest 0.5 cm in a standing position without shoes. BMI will be computed as body weight (kilograms) divided by height squared (centimeters squared). Waist circumference will be evaluated at the narrowest point above the hips with an unstretched tape measure.

### Statistical analysis

Statistical tests of the outcome measures will be performed using SPSS (version 22.0; SPSS Inc., Chicago, IL, USA). The normality of distribution will be examined and confirmed by the Kolmogorov–Smirnov test. All results will be expressed as mean ± SD. Categorical variables will be presented as frequencies and percentages. The chi-square test will be used to test for differences between categorical variables. Baseline mean differences will be tested using one-way analysis of variance (ANOVA). Analysis of covariance (ANCOVA) will be used to identify differences between the four treatment arms at the end of study, adjusting for baseline values and covariates. The comparison of mean values will be done within groups after the intervention period using paired-sample *t* tests. Bonferroni corrections will be used in pairwise comparisons of the values after the intervention. *P* < 0.05 will be considered statistically significant.

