**Methods:**

We will conduct an 8-week, double-blind, randomized, placebo-controlled clinical trial, in a factorial design, to evaluate the individual effects of vitamin D and magnesium, and co-supplementation of them, on mood, serum level of BDNF, inflammation, and SIRT1 in 108 obese women.

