### Objectives and hypotheses of the study

The primary objective of the present study is to assess the effects of vitamin D_3_ and magnesium co-supplementation in obese women on readouts of mood, serum levels of 25(OH)-D, magnesium, BDNF, inflammatory biomarkers (hs-CRP, TNF-α, IL-6), and sirtuin 1 levels. For controlling of confounder factors, the study will evaluate anthropometric indices (weight, body mass index, and waist circumference), dietary intake of energy and macronutrients, and physical activity levels in the women at baseline and at the end of the study.

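### The trial is sized for one two-arm hs-CRP contrast, but no contrast is named to decide the co-supplementation objective, and Bonferroni over all pairs would cut its power from the stated 80% to about 55%

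*Protocol article*

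**What the plan says.** Only the protocol article is available; a statistical analysis plan may exist but is not shown.

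- **Objective.** Under Objectives and hypotheses: "The primary objective of the present study is to assess the effects of vitamin D_3_ and magnesium co-supplementation in obese women". No comparator is given. The abstract is wider and says the trial is "to evaluate the individual effects of vitamin D and magnesium, and co-supplementation of them".
- **Design.** The Design section calls the trial factorial. The Randomization section lists four arms: both supplements, vitamin D alone, magnesium alone, and double placebo.
- **Sample size.** The section takes α = 0.05, β = 0.20, hs-CRP as the primary variable, a standard deviation of 1570.5 ng/ml and a value of 1250.0 ng/ml that it calls the mean. It arrives at 25 per group, and with attrition "27 participants will be recruited for each group, giving a total of 108 obese women". It does not say which two arms the calculation compares.
- **Analysis.** The Statistical analysis section says "Analysis of covariance (ANCOVA) will be used to identify differences between the four treatment arms at the end of study", adjusted for baseline values and covariates. It adds that "Bonferroni corrections will be used in pairwise comparisons of the values after the intervention", without listing the pairs or their number. The paired *t* tests within arms make no between-arm comparison.

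**The concern.** Three pairwise contrasts involve the combined arm: against double placebo, against vitamin D alone, and against magnesium alone. The first asks whether the combined regimen does anything. The other two, taken together, ask whether giving both is better than giving one. The article does not say which of these settles its primary objective.

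Two things are at stake. First, the sample size belongs to a single contrast at 0.05, while the analysis applies a stricter threshold to an unlisted set of pairs, so the power stated may not be the power delivered. Second, a report could support a co-supplementation benefit from any significant combined-arm pair, including pairs that are truly different when one of the two supplements contributes nothing.

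**Working it through.** **Inputs.** From the Sample size section: SD = 1570.5 ng/ml, 1250.0 ng/ml, α = 0.05, power 0.80, 25 per group before attrition. From the Randomization section: four arms.

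**Assumptions.** 1250 is read as the between-group difference, the test is two-sided, the outcome is normal, baseline adjustment brings no gain, and Bonferroni covers all 4 × 3 / 2 = 6 pairs.

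**1. Reproduce the stated size.** n per group = 2(z₁₋α/₂ + z₀.₈₀)² (SD/Δ)².
- One contrast at two-sided 0.05: 2(1.960 + 0.842)² (1570.5/1250)² = 24.8, rounded up to 25. This matches.
- One-sided 0.05 gives 19.5, that is 20.
- Two-sided 0.05/6 gives 38.2, that is 39.
- Two-sided 0.05/3 gives 34.

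Of these, only the single unadjusted two-sided contrast gives the stated 25.

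**2. Power for combined versus double placebo.** The standard error at 25 per arm is 1570.5 × √(2/25) = 444.2, so Δ/SE = 1250/444.2 = 2.81.
- At 0.05: Φ(2.81 − 1.96) = 0.80.
- At 0.05/6: Φ(2.81 − 2.64) = 0.57. With the *t* distribution on 96 degrees of freedom, simulation gives 0.55.
- At 0.05/3: 0.66 by the normal formula.
- With all 27 per arm retained, the normal formula gives 0.83 at 0.05 and 0.61 at 0.05/6.

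**3. What a significant combined-arm pair would mean.** Simulated four-arm trials, 25 per arm, effect 1250/1570.5 = 0.80 SD, Bonferroni over six:

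| Truth | Combined v placebo | Combined v vitamin D | Combined v magnesium | Any of the three |
|---|---|---|---|---|
| No effect | 0.9% | 0.8% | 0.8% | 2.3% |
| Only vitamin D works | 55% | 0.8% | 55% | 71% |
| Half the effect each, additive | 55% | 10% | 10% | 57% |
| Only the combination works | 55% | 55% | 55% | 79% |

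In the second row magnesium adds nothing, yet some combined-arm contrast is significant in about 71% of trials, almost always against placebo or against magnesium alone. Under the full null, any of the six pairs is significant in about 4% of trials, so Bonferroni does its job within one outcome.

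**4. The proposed sequence.** Combined versus double placebo at 0.05 has 79 to 80% power. Added benefit is claimed only if that contrast and both single-arm contrasts are significant at two-sided 0.05 in favour of the combination. In simulation this happens in about 14% of trials with additive halves and about 60 to 61% if only the combination works. If only vitamin D works, it happens in at most 0.05/2 = 2.5%, because combined versus vitamin D alone is then a true null.

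**5. Sensitivity to baseline adjustment.** For 25 per arm to give 80% power at 0.05/6, ANCOVA would have to remove 1 − 25/38.2 = 35% of the variance. The article offers no figure for this.

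**The case against.** The strongest reply is that ranking contrasts is analysis-plan detail, and the article already describes a coherent method: baseline-adjusted ANCOVA with corrected pairwise comparisons. The trial is called placebo-controlled and nowhere claims synergy, so the natural reading of the objective is combined versus double placebo. On that reading a positive result when only vitamin D works is correct, because the combined regimen does differ from placebo. The proposed fix makes that same contrast decisive and raises its chance of significance in that scenario from about 55% to about 80%. If all pairs are compared, vitamin D alone versus placebo is also tested, so the responsible component may show itself.

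Much of this stands. Bare silence about a hierarchy would not be a finding. What remains is that two things the article does state do not fit: a sample size for one contrast at 0.05, and a Bonferroni correction over pairwise comparisons. The natural reading sharpens this, since the contrast it selects is the one that loses power.

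A reader might also infer more than the text supports:
- *That the plan inflates false positives.* It does not within one outcome; about 4% of null trials give any significant pair.
- *That the contrasts lead to opposite conclusions.* Beating placebo and not being shown to beat vitamin D alone are compatible results.
- *That the article commits to all six pairs.* It lists none; six is the usual default for four arms, and a shorter list would cost less power.

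**Conclusion.** The point holds as a mismatch between objective, sample size and stated analysis. The article sizes the trial for one unnamed two-arm contrast, names none as deciding its primary objective, and applies a correction under which combined versus double placebo has about 55% power if six pairs are tested (about 66% if three), against the stated 80%. These figures assume that 1250 is the between-group difference and that baseline adjustment brings no gain; a strong baseline correlation would narrow the gap.

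It also leaves undefined what would count as an added benefit of giving both supplements. Two of the three combined-arm contrasts are truly non-null when only one supplement works, so a significant pair cannot by itself carry that claim. The tempting stronger conclusion, that a significant combined-versus-placebo result would then be false, is not supported: it is a valid finding about the regimen. This should be corrected, but it is not a failure of error control.

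**What to change.** In the Objectives and Statistical analysis sections:

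1. Name the deciding contrast: combined versus double placebo on week-8 hs-CRP, baseline-adjusted ANCOVA, two-sided 0.05. The Sample size section already makes hs-CRP the primary variable. State there that 25 per group refers to this contrast and that 1250.0 ng/ml is its assumed difference, if that is what was meant.
2. If it is significant, test combined versus vitamin D alone and combined versus magnesium alone, each at two-sided 0.05. Claim added benefit over a single supplement only if both are significant in favour of the combination. Because both must reject, no split of alpha is needed.
3. Otherwise, after a significant first step, conclude only that the combined regimen differs from placebo and that the contribution of each component is not established.
4. Label the other three pairs (each single supplement versus placebo, and one single supplement versus the other) secondary, list them, and keep Bonferroni for them.

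This takes a few sentences and no extra participants or data. Recruitment began in October 2019 according to the Trial status section, so it would be an amendment and should be fixed before unblinding. The price is that the individual-effect comparisons become secondary and the added-benefit claim has low power at 25 per group: about 14% with additive halves and about 60 to 61% if only the combination works. The protocol should say so.

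### The trial is declared 2×2 factorial, but the planned analysis specifies neither the marginal effect of each supplement nor the vitamin D × magnesium interaction

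*Protocol article*

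**What the plan says.** The Design section of the protocol article states: "We will conduct an 8-week, double-blind, randomized controlled trial in a factorial design". The Methods paragraph of the abstract gives the purpose as "to evaluate the individual effects of vitamin D and magnesium, and co-supplementation of them". Under Objectives the emphasis is on the combination: "The primary objective of the present study is to assess the effects of vitamin D_3_ and magnesium co-supplementation in obese women".

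The Randomization section sets out all four cells of a 2×2: both active, vitamin D with magnesium placebo, magnesium with vitamin D placebo, and double placebo ("The 108 participants who meet the criteria will be allocated as such into four treatment groups").

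The Statistical analysis section then states: "Analysis of covariance (ANCOVA) will be used to identify differences between the four treatment arms at the end of study", adjusted for baseline values and covariates. It adds paired t tests within groups and Bonferroni-corrected pairwise comparisons after the intervention. It names no vitamin D factor, no magnesium factor and no interaction term, and it does not say how many pairs are compared.

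The Background describes magnesium as a cofactor at several steps of vitamin D metabolism. It adds that the active vitamin D metabolite stays low in magnesium deficiency even when vitamin D is taken.

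**The concern.** A factorial layout offers two things that a plain four-arm trial does not. If the supplements act independently, each effect can be estimated by comparing everyone who received the supplement with everyone who did not. It also allows a direct estimate of whether the effect of one supplement depends on the other. The planned tests take up neither.

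The second omission matters more here, because the cofactor argument in the Background is an argument for an interaction. A pairwise test compares two arms, whereas the interaction is a contrast among all four. If the combination beats double placebo and neither single supplement does, that pattern says nothing about synergy, yet without an interaction estimate beside it, it could be taken that way.

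The article does state which tests will be used, and they do not match the declared design. This is therefore more than the brevity of a journal article.

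**Working it through.** **Inputs (Sample size section).** SD 1570.5 ng/ml and 1250.0 ng/ml for hs-CRP, α = 0.05, β = 0.20; 25 per group required and 27 recruited. The 1250 figure is called a mean, but the stated size follows only if it is read as the difference to detect.

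**The plan's own figure.** n = 2 × [1570.5 × (1.960 + 0.842) / 1250]² = 24.78, rounded up to 25. This reproduces the plan with a two-sided α and one arm against one arm. The one-sided version gives 20.

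**Standard errors with n = 25 per cell.**

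| Contrast | Formula | SE (ng/ml) |
|---|---|---|
| Pair of arms | SD × √(2/n) | 444 |
| Main effect (50 v 50) | SD × √(1/n) | 314 |
| Interaction (difference of differences) | SD × √(4/n) | 628 |

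The variance of a pair is twice that of a main effect.

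**Power at 1250 ng/ml.** Noncentral t with 4 × (25 − 1) = 96 df and noncentrality 1250/SE, no gain from baseline adjustment:

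| Contrast | α | Noncentrality | Power |
|---|---|---|---|
| Main effect, no interaction | 0.05 | 3.98 | 97.6% |
| Pair, uncorrected | 0.05 | 2.81 | 79.6% |
| Pair, Bonferroni over 3 | 0.05/3 | 2.81 | 64.7% |
| Pair, Bonferroni over 6 | 0.05/6 | 2.81 | 55.0% |
| Interaction of 1250 ng/ml | 0.05 | 1.99 | 50.4% |

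If all 27 per cell are analysed, the six-pair figure becomes 59.4%. A normal approximation gives 97.8%, 80.3%, 66.3%, 57.0% and 51.2% for the five rows, so the choice of method is not important.

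**If only the combination works, by 1250 ng/ml.** Each main effect averages 1250 and 0, that is 625 ng/ml. Noncentrality is 625/314 = 1.99, so power is 50.4%. The combination-versus-double-placebo pair has 55.0% at α/6.

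**If the effects are purely additive, 0.5 SD each (785 ng/ml).**
- Main effect: 785/314 = 2.50, power about 70%.
- Single supplement v double placebo at α/6: 785/444 = 1.77, power 18%.
- Combination v double placebo at α/6: 1570.5/444 = 3.54, power about 80%.

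With no interaction at all, the combination would then usually reach significance while each single supplement usually would not.

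**Same model.** In a simulated data set with 25 per cell and one baseline covariate, the four-arm ANCOVA and the ANCOVA with vitamin D, magnesium and their product gave the same residual sum of squares (96.77) and the same residual df (95). The missing quantities are therefore contrasts of the model already planned.

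**The case against.** The strongest reply is that the planned pairwise comparisons already answer the question in the abstract. Vitamin D alone against double placebo estimates the individual effect of vitamin D, magnesium alone does the same for magnesium, and the combination against double placebo estimates co-supplementation. The primary objective concerns the combination, and no stated objective is to test synergy. Arm-level comparison also fits the sample size, which was derived for one arm against another, and it is a defensible choice when an interaction is plausible. All of this stands. A reader might infer that the individual effects are never estimated; the documents do not support that. What is unplanned is the marginal main effects and the interaction.

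A reader might also infer that half the data go unused. That is true only of the arm means in a single-supplement comparison. All four arms inform the residual variance and the covariate slopes, and the interaction uses all four cells.

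Third, the smallest difference detectable with 80% power is 0.57 SD for an uncorrected main effect and 1.00 SD for a pair at α/6. It is tempting to credit that whole gap to the factorial layout. An uncorrected pair detects 0.80 SD, so the rest is a multiplicity penalty that depends on six comparisons, a number the plan does not give.

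Finally, contrasts can be left to a fuller document. That would excuse silence, but this section names its tests, and they are arm-level ones.

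**Conclusion.** The point holds as a mismatch between the declared design and the specified contrasts. At the same α = 0.05 and the planned difference, leaving out the main effects forgoes 97.6% against 79.6% power, but only if there is little interaction. If only the combination works, the main effects have about 50% power and are no better than the planned comparison. The more lasting loss is the interaction estimate. It would be imprecise (SE 628 ng/ml), but it is the only quantity that speaks to the cofactor rationale.

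It would go too far to say that the trial cannot answer its stated question: the pairwise tests do address the single and combined effects against double placebo.

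The figures assume a two-sided α, 1250 ng/ml as the difference, 25 evaluable per cell and equal variances. Adjustment for baseline would raise every power figure by an amount that the document does not allow one to calculate.

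**What to change.** In the Statistical analysis section:

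1. Express the ANCOVA as vitamin D (yes/no), magnesium (yes/no) and vitamin D × magnesium, adjusted for baseline and for the covariates already planned.
2. Report both main effects and the interaction with 95% confidence intervals. Define each main effect as the average over the two levels of the other supplement; under 0/1 coding the single-factor coefficients are effects against double placebo instead.
3. Keep three contrasts with double placebo (combination, vitamin D alone, magnesium alone) under the stated Bonferroni correction, and fix the number of comparisons in advance. With three, power at 1250 ng/ml is 64.7%, so the sample size section should not imply 80% for a corrected pair.
4. State that the interaction is reported as an estimate because the trial is not powered for it, and that a significant combination beside non-significant single supplements is not evidence of synergy.

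The cost is wording: no extra participants or data, and the same fitted model. The change should be made before unblinding, since contrasts added later would be post hoc. The downside is that the main effects must always be read beside the interaction estimate.
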